## Abstract

**Introduction:**

Heart failure (HF) remains a leading cause of hospitalization and death in Germany, significantly impairing patients’ quality of life (QoL) despite advances in therapy. Structured, multidisciplinary care programs may improve long-term outcomes. HI-PLUS is a pragmatic trial investigating whether a complex intervention can improve QoL in HF patients. We describe the trial design and pilot feasibility study findings.

**Methods and results:**

HI-PLUS is a cluster-randomized, parallel-arm controlled trial (DRKS00031997) targeting 56 clusters, each comprising a cardiology practice and up to five general practitioners (GPs), targeting 1350 patients. The control arm receives guideline-recommended care. The intervention adds five elements: (a) care supported by specially trained non-physician staff HF qualified (HF-MPA); (b) accredited HF-MPA training curriculum certified by the German Society of Cardiology; (c) eHealth platform for telemonitoring and symptom reporting; (d) portable telemedical devices, if needed; and (e) enhanced communication between cardiologists and GPs facilitated by HF-MPAs and the eHealth platform. The primary endpoint is change in HF-specific QoL after 12 months, measured by the Kansas City Cardiomyopathy Questionnaire Overall Summary Score (KCCQ-OSS). A pilot feasibility study that was conducted prior to commencement of patient recruitment confirmed the feasibility and acceptability of the proposed trial procedures.

**Conclusion:**

The HI-PLUS trial addresses recognized gaps in HF care. If effective, it could serve as a scalable model for integrated HF care throughout Germany.

**Graphical Abstract:**

**Figure Figa:**
[figure not shown]

**Supplementary Information:**

The online version contains supplementary material available at 10.1007/s00392-026-02904-8.

## Introduction

Although the incidence of heart failure (HF) has remained relatively stable, the prevalence continues to rise as advances in evidence-based therapies and care prolong survival [1]. Yet, recurrent hospitalizations remain very frequent, placing a heavy burden on healthcare systems and diminishing patients’ quality of life (QoL) [2]. Accordingly, preserving or improving health-related QoL is thus a core therapeutic aim in chronic HF care, alongside traditional clinical outcomes [3, 4].

Contemporary European guidelines recommend that patients with HF participate in a multidisciplinary management program [2]. Case-management and multidisciplinary approaches, particularly those led by specialist nurses, can reduce mortality and HF readmission rates [5]. Such programs can be clinic-based, home-based, or hybrid, and may incorporate telemonitoring. To be effective, they should be patient-centered, address comorbid conditions, enhance self-management skills, and be tailored to the resources of the healthcare system and to individual patient needs [5, 6]. Telemonitoring, for instance, has been shown to sustain care quality, enable timely interventions, and reduce the need for travel and in-person visits [7], in particular for patients who live far away from their cardiologist [8].

In Germany, HF outpatient care is primarily delivered by general practitioners (GPs), although outpatient cardiologists are also a component of the patient care pathway [3]. Currently, there is no comprehensive nationwide disease management program (DMP) to ensure standardized and coordinated care [3]. This fragmentation contributes to suboptimal implementation of guideline-recommended treatment, including underuse of evidence-based pharmacotherapy and limited communication across care sectors. Importantly, providing the time-intensive, individualized care that many HF patients require remains a challenge in outpatient practice [2]. Prior initiatives—such as the Interdisciplinary Network for Heart Failure (INH) study, which evaluated the impact of a nurse-led disease management program on mortality and morbidity in patients with heart failure [9, 10], and the Telemedical Interventional Management in Heart Failure II (TIM-HF2) trial, which assessed the effect of a structured remote patient management system on unplanned hospital admissions for cardiovascular reasons and mortality [11, 12]—demonstrated favorable effects yet underscored the ongoing need for scalable, patient-centered, evidence-based HF care across Germany.

In 2018, the Federal Joint Committee (G-BA) of Germany proposed a DMP for HF patients (DMP-HI) [13]. In 2021, the Institute for Quality and Efficiency in Health Care (IQWiG) subsequently identified areas for updating and recommended additional measures [14]. The IQWiG also provided an evidence mapping on structured support interventions for HF monitoring, intended to inform targeted decisions on potentially useful additions to the DMP-HI [15]. In 2024, the G-BA updated the DMP-HI to integrate telemonitoring [13], which is reimbursed by statutory health insurance since January 2022 for patients with NYHA functional class II or III and guideline-based treatment [16].

### Aim of the trial

We report the design and results of the pilot feasibility study of the ongoing HI-PLUS trial in Germany, which tests whether a structured, evidence-based care and case-management program, augmented by an eHealth platform, improves health-related QoL compared with usual care.

## Methods

### Trial design and randomization

The HI-PLUS trial is a pragmatic, parallel-arm, cluster-randomized study being conducted between June 2023 and June 2026. Cardiology practices (CPs) serve as the units of randomization because the intervention is delivered at the practice level and involves coordination with affiliated general practitioners (GPs). Clusters are generated by a single CP and up to five cooperating GPs and are assigned in a 1:1 ratio to either the intervention or control arm using stratified block randomization generated by PASS 2020 software. Stratification factors include the presence of a HF medical practice assistant (HF-MPA) at baseline. This design permits comparison of the complex intervention with usual care while accommodating the realities of practice-level implementation and minimizing contamination. Further information about the trial organization is listed in Supplementary Table S1.

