### Setting and recruitment

CPs were recruited through professional associations, specifically the German Association of Registered Cardiologists (BNK). The target was 56 CPs (28 per group) working with approximately 280 GPs. Eligibility required CPs to consent to random allocation, deliver care per assignment, train 1–3 non-physician staff members if randomized to the intervention, and coordinate the network together with approximately 2 to 7 GPs (mean 5). CPs in the control arm that already employed a HF-MPA can participate provided a formal HF care pathway has not yet been implemented. A care pathway is considered implemented if the HF-MPA actively acts as an interface in the following manner between the cardiologist, the GP, the hospital, and the patient: (a) records and assesses HF symptoms, liaises with the supervising cardiologist, and ensures implementation of the recommendations is implemented; and/or (b) monitors the therapy (via telephone or telemonitoring) and provides outpatient coaching as required. The project team surveys CPs quarterly to ascertain whether a HF care pathway has been implemented through completion of an appropriate questionnaire; discovery of an implemented care pathway triggers drop-out from the control arm. It was estimated that approximately 25% of all CPs have already employed a HF-MPA without yet implementing a HF care pathway.

Practice catchment areas should not overlap, and no other HF care program should be offered regularly to participating patients to reduce contamination bias. Patients in the control group receive usual care concordant with national care guidelines [3] and a trial-specific assessment of primary and secondary outcomes. The trial protocol adheres to the CONSORT extension for cluster-randomized trials [17, 18] and was registered at the German Clinical Trials Register (DRKS00031997).

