### Sample size

The trial is powered to detect a 5-point between-group difference in KCCQ-OSS from baseline to 12 months, a threshold regarded as clinically meaningful and associated with a 10% risk reduction in mortality and HF-related rehospitalization [4, 23–25]. Similar or even greater improvements have been observed in previous therapy optimization studies [26]. The sample size calculation is based on a two-sided *t*-test with degrees of freedom based on the number of clusters, with the significance level set at 5%.

In the INH study, an intraclass correlation coefficient (ICC) of 0.003 was reported for the change in KCCQ-OSS between baseline and 12-month follow-up [10]. Given that the clusters in the INH study comprised cardiology departments within one region, we assume a more conservative ICC of 0.01 for the current trial. For estimating the KCCQ-OSS standard deviation (SD), we refer to the study by Jayaram, which reported an SD of 25.4 points for the change over 6 months [26]. Since the SD remained relatively stable during this period, we assume an SD of 25.4 points after 12 months as well. We also assume a variation in the number of patients per cluster of 0.5. With an ICC of 0.01, an average of 21 HF patients per cluster (*n* = 1050) is needed to detect a significant 5-point difference with 80% power. Considering an expected dropout rate of 20% for patients and 10% for practices, the final sample size is 56 clusters with 1350 patients. Each cardiologist is expected to collaborate with 2–5 GPs, involving up to 280 GPs in total. The sample size was conducted using the software PASS 2020.

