### Statistical methods

Analyses will follow the intention-to-treat principle using SAS 9.3 or R. The significance level is defined at 5%. Descriptive analyses of the primary and secondary endpoints will be carried out. The primary analysis will use a univariable linear mixed-effects model with random effects for clusters (CPs) and fixed effects for group (intervention vs control). A multivariable mixed-effects model will secondarily adjust for potential confounders, e.g., age, sex, NYHA functional class, time since diagnosis, care dependency, and living status. A predefined sensitivity analysis will be performed to account for the timing of the anticipated DMP-HI implementation, whose exact start date had not been determined at the time of trial approval. Specifically, a mixed-effects model will be applied to the primary outcome, including both groups and duration of DMP-HI use as fixed effects, while modelling CP as a random effect. If a CP has not participated in the DMP-HI by the end of data collection, duration will be set to zero. If no CP has adopted the DMP-HI 4 weeks before study end, this analysis will be omitted. In addition, a subgroup analysis will evaluate the primary endpoint based on the presence/absence of a trained HF-MPA prior to trial start. Analyses of secondary outcomes will be conducted using univariable and multivariable mixed-effects models. To assess the potential influence of GPs on study outcomes, an additional sensitivity analysis will be run to account for clustering effects at the GP level. This will involve the use of a mixed-effects model with the intervention as a fixed effect and both cardiologists and GPs as random effects.

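### The primary model omits the randomisation stratum (baseline HF-MPA presence), so the test is conservative if that factor is prognostic

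*Protocol article*

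**What the plan says.** Under Trial design and randomization, practices are "assigned in a 1:1 ratio to either the intervention or control arm using stratified block randomization", and "Stratification factors include the presence of a HF medical practice assistant (HF-MPA) at baseline". The verb leaves open whether other factors were used.

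Under Statistical methods, "The primary analysis will use a univariable linear mixed-effects model", with the practice as random effect and group as the only fixed effect. A secondary multivariable model adjusts for "potential confounders, e.g., age, sex, NYHA functional class, time since diagnosis, care dependency, and living status". The HF-MPA factor appears in that section only once: "a subgroup analysis will evaluate the primary endpoint based on the presence/absence of a trained HF-MPA prior to trial start".

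Setting and recruitment gives the expected prevalence of the factor: "approximately 25% of all CPs have already employed a HF-MPA without yet implementing a HF care pathway". Under Sample size, "The trial is powered to detect a 5-point between-group difference in KCCQ-OSS from baseline to 12 months".

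**The concern.** Stratified allocation balances the arms on HF-MPA presence. Differences between strata therefore drop out of the true sampling variance of the treatment contrast. A model with group alone does not know this: it estimates the stratum difference as part of the variance between practices and carries it into the standard error. If the factor is prognostic, the reported standard error exceeds the real one, the confidence interval is wider than it need be, and the test rejects less often than its nominal level.

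What is at stake is precision and power, in a trial planned at 80% with little reserve. The subgroup analysis and the secondary adjusted model do not alter the primary test.

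**Working it through.** **Inputs.** From Sample size: target difference 5 points; SD 25.4; ICC 0.01; variation in cluster size 0.5 (read as a coefficient of variation); 21 patients per cluster and n = 1050, hence 1050/21 = 50 clusters; two-sided 5% t-test with degrees of freedom from the clusters, 50 − 2 = 48. From Setting and recruitment: prevalence of the factor p = 0.25. *Assumed, not in the document:* the difference γ in mean KCCQ-OSS change between practices with and without an HF-MPA, and a block size of 4 in the simulation.

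**1. The plan's own figure.** Design effect = 1 + ((0.5² + 1) × 21 − 1) × 0.01 = 1.2525. SE = 25.4 × √(4 × 1.2525/1050) = 1.755. With noncentrality 5/1.755 = 2.85 and 48 df, power is 79.7% (80.0% with a relative-efficiency design effect of 1.245). The stated 80% reproduces.

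**2. Variance due to the stratum.** It is p(1 − p)γ² = 0.1875γ². The planned between-cluster variance is 0.01 × 25.4² = 6.45. The result depends on whether the stratum variance comes on top of this figure or is already inside it.

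**3. Case A: γ on top of a within-stratum ICC of 0.01.** At γ = 5 the stratum adds 0.1875 × 25 = 4.69. Between-cluster variance becomes 6.45 + 4.69 = 11.14 and total variance 645.16 + 4.69 = 649.85, so the ICC is 11.14/649.85 = 0.017. The group-only SE is √(649.85 × 1.433 × 4/1050) = 1.883, against a true value of 1.755. The analytic results for the unadjusted test are:

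- γ = 2.5: type I error 4.6%, power 78.7%
- γ = 5: 3.6%, 75.4%
- γ = 10: 1.4%, 61.9% (total ICC 0.038)

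A simulation of the same case used a REML random-intercept model, unequal cluster sizes and stratified blocks, with 6000 null and 3000 alternative runs:

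| γ | Type I, without factor | Type I, with | Power, without | Power, with |
|---|---|---|---|---|
| 0 | 4.3% | 4.3% | 79.9% | 79.7% |
| 2.5 | 4.5% | 4.8% | 79.1% | 80.2% |
| 5 | 4.2% | 4.9% | 76.8% | 80.7% |
| 10 | 1.9% | 4.7% | 63.1% | 78.7% |

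The Monte Carlo standard error is about 0.3 percentage points for type I error (√(0.05 × 0.95/6000)) and 0.7 for power (√(0.8 × 0.2/3000)). At γ = 5 the mean model SE is 1.86 against an empirical SD of 1.75. A simpler run with equal cluster sizes puts the loss at γ = 3 at about 1 percentage point of power.

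**4. Case B: the planned ICC of 0.01 already contains the stratum difference.** Then γ cannot exceed √(6.45/0.1875), about 5.9 points. The unadjusted SE stays at 1.755 and the true SE falls.

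- γ = 5: within-stratum between-cluster variance 6.45 − 4.69 = 1.76, true SE 1.615, type I error 3.4%, power 81.6% unadjusted and 85.8% adjusted.
- At the limit: true SE 1.56, type I error 2.8%, power 82.4% unadjusted and 88.1% adjusted.

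**5. Cost of adjusting for a factor that does not matter.** Degrees of freedom go from 48 to 47 and analytic power from 79.74% to 79.71%.

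**The case against.** The strongest reply is that the harm rests on a number the article does not supply. A 5-point stratum difference would equal the whole target treatment effect. The text also gives reasons to expect less. Control practices that already have an HF-MPA may take part only without an implemented care pathway and leave the arm if one is found, while every intervention practice works with a trained HF-MPA. The ICC of 0.003 that the article cites from the INH study would cap the difference at √(0.003 × 25.4²/0.1875), about 3.2 points. The sample size itself assumes an unadjusted t-test, so analysis and power calculation agree. The error is also on the safe side. At γ = 5 the simulated type I error of 4.2% is hardly below the 4.3% seen with no prognostic effect at all.

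All of this stands as to size. It does not remove the mismatch, because the article states both the stratification and the group-only model; this is not a detail left to an unseen analysis plan.

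A reader might also infer several stronger points that the article does not support:

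- **That the sponsor regarded the factor as prognostic.** No reason for stratifying is given; balance for the planned subgroup analysis would explain it equally well.
- **That the factor is excluded from the multivariable model.** The covariates are given only as examples, so it is unnamed rather than excluded.
- **That the subgroup analysis lacks an interaction test.** The article does not describe how that analysis is modelled.

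**Conclusion.** The mismatch between design and primary model is real and its direction is certain: no bias, no excess of false positives, and a conservative test if the stratum is prognostic. The consequence is conditional:

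- **About 3 points or less:** negligible.
- **5 points on top of a within-stratum ICC of 0.01:** roughly 4 percentage points of power (about 77% against 81%), at a total ICC of about 0.017.
- **Stratum difference already inside the planned ICC of 0.01:** planned power is kept, and what is forgone is extra power, up to 88% instead of at most 82.4%.

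It would be tempting to say outright that the intervals are too wide and power is being lost, or to quote the large losses seen at stratum differences well above 5 points. Neither is supported. The prognostic effect is unknown, and differences beyond about 5.9 points imply more between-practice variance than the planned ICC allows. This is a worthwhile improvement at almost no cost, not a threat to validity.

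**What to change.** Add baseline HF-MPA presence, and any other stratification factor used in the allocation, as a fixed effect in the primary mixed model and in the corresponding mixed models for secondary outcomes. State the full list of stratification factors. The univariable model can be kept as a sensitivity analysis.

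Prespecify the change before outcomes are analysed by arm; the article schedules the last follow-up for June 2026 and reporting for September 2026. No new data are needed, because the factor had to be known for allocation. The cost is a sentence in the analysis plan and one cluster-level degree of freedom for this factor, with correspondingly more if further stratification factors were used.

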### Setting and recruitment

CPs were recruited through professional associations, specifically the German Association of Registered Cardiologists (BNK). The target was 56 CPs (28 per group) working with approximately 280 GPs. Eligibility required CPs to consent to random allocation, deliver care per assignment, train 1–3 non-physician staff members if randomized to the intervention, and coordinate the network together with approximately 2 to 7 GPs (mean 5). CPs in the control arm that already employed a HF-MPA can participate provided a formal HF care pathway has not yet been implemented. A care pathway is considered implemented if the HF-MPA actively acts as an interface in the following manner between the cardiologist, the GP, the hospital, and the patient: (a) records and assesses HF symptoms, liaises with the supervising cardiologist, and ensures implementation of the recommendations is implemented; and/or (b) monitors the therapy (via telephone or telemonitoring) and provides outpatient coaching as required. The project team surveys CPs quarterly to ascertain whether a HF care pathway has been implemented through completion of an appropriate questionnaire; discovery of an implemented care pathway triggers drop-out from the control arm. It was estimated that approximately 25% of all CPs have already employed a HF-MPA without yet implementing a HF care pathway.

Practice catchment areas should not overlap, and no other HF care program should be offered regularly to participating patients to reduce contamination bias. Patients in the control group receive usual care concordant with national care guidelines [3] and a trial-specific assessment of primary and secondary outcomes. The trial protocol adheres to the CONSORT extension for cluster-randomized trials [17, 18] and was registered at the German Clinical Trials Register (DRKS00031997).

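### A control-arm-only drop-out rule that acts after allocation is not reconciled with the intention-to-treat analysis, and would tend to favour HI-PLUS if dropped practices leave the data

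*Protocol article*

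**What the plan says.** Under Setting and recruitment, the protocol article sets a participation condition for control practices: "CPs in the control arm that already employed a HF-MPA can participate provided a formal HF care pathway has not yet been implemented". It then adds continuing surveillance: "The project team surveys CPs quarterly to ascertain whether a HF care pathway has been implemented". The consequence of a positive finding is that "discovery of an implemented care pathway triggers drop-out from the control arm". No corresponding rule is stated for intervention practices.

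A pathway counts as implemented when the HF-MPA actively acts as the interface between cardiologist, GP, hospital and patient in one or both of two ways. The first is recording and assessing symptoms, liaising with the supervising cardiologist and seeing that recommendations are carried out. The second is monitoring therapy by telephone or telemonitoring, with coaching as required.

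The same section describes the comparator: "Patients in the control group receive usual care concordant with national care guidelines". It also estimates that "approximately 25% of all CPs have already employed a HF-MPA without yet implementing a HF care pathway".

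The Statistical methods section states "Analyses will follow the intention-to-treat principle using SAS 9.3 or R" and specifies a "univariable linear mixed-effects model with random effects for clusters (CPs) and fixed effects for group (intervention vs control"). The Sample size section allows for 10% of practices dropping out. The Results section places group allocation after contract signature, so the quarterly survey comes after randomisation.

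**The concern.** Whether a control practice builds a pathway during the trial is a post-randomisation event, and the event concerns the care its patients receive. Intention-to-treat keeps randomised clusters in the arm to which they were allocated, whatever care they later deliver. If the drop-out rule also takes a practice and its patients out of the analysis, the remaining control arm is no longer the randomised one. The part removed is the part whose care is closest to the intervention.

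At stake is the primary contrast in KCCQ-OSS change. The trial is described as pragmatic and compares HI-PLUS with usual care. A control arm from which pathway-adopting practices have been taken out represents usual care without adoption, which is a different comparator.

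**Working it through.** **1. Does the text settle what happens to the data?** Three places bear on it.
- Setting and recruitment: discovery leads to drop-out from the control arm. Nothing is said about patients already enrolled.
- Statistical methods: intention-to-treat, with no exception for such practices.
- Sample size: n = 1050 at 21 patients per cluster is 1050 / 21 = 50 clusters. With 10% practice drop-out, 50 / 0.9 = 55.6, rounded up to 56. Dropped practices are therefore budgeted as clusters that must be replaced, which suggests their data are expected to be lost. It does not define an analysis set.

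So exclusion is the natural reading, but it is inferred.

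**2. The plan's own figure.** Inputs from the Sample size section: difference 5, SD 25.4, ICC 0.01, variation in cluster size 0.5 (read as a coefficient of variation), 21 patients per cluster, two-sided 5% t-test with cluster-based degrees of freedom.
- Design effect = 1 + ((1 + 0.5²) × 21 − 1) × 0.01 = 1.2525.
- Standard error with 25 clusters per arm = 25.4 × √(1.2525 × 2 / 525) = 1.7545.
- Noncentrality = 5 / 1.7545 = 2.85, with 48 degrees of freedom; power = 79.7%.

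The stated 80% reproduces. The sample size is therefore not in question on this point.

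**3. Size of the effect if dropped practices are excluded.** Let q be the share of control practices removed and f the fraction of the 5-point effect that their own pathway delivers. Then:
- as-allocated contrast = 5 × (1 − q × f);
- contrast after removal = 5;
- inflation = 5 × q × f.

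The documents give neither q nor f. The values below are assumptions. The upper value of q borrows the 25% estimate of practices that have an HF-MPA but no pathway, which is not a trigger rate.

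| q | f | As allocated | After removal | Inflation |
|---|---|---|---|---|
| 10% | 50% | 4.75 | 5.00 | 0.25 (5%) |
| 10% | 100% | 4.50 | 5.00 | 0.50 (11%) |
| 25% | 50% | 4.38 | 5.00 | 0.63 (14%) |
| 25% | 100% | 3.75 | 5.00 | 1.25 (33%) |

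**4. If neither the intervention nor the pathway has an effect.** Bias then arises only if adoption is related to the practice's outcome level. The between-practice SD is 25.4 × √0.01 = 2.54. With q = 10% and correlation ρ between adoption and outcome level, the shift is ρ × 2.54 × φ(z) / (1 − q), where z is the 90th normal percentile and φ the standard normal density. Positive values favour HI-PLUS. Type I error is for 28 versus 25 practices with about 19.3 analysed patients each (1350 × 0.8 / 56).
- ρ = 0: shift 0, type I error 5.0%.
- ρ = 0.5: shift +0.25, type I error 5.2%.
- ρ = 1: shift +0.50, type I error 5.9%.
- ρ = −0.5: shift −0.25, type I error 5.2%.

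The direction is thus not fixed by the design alone.

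**The case against.** The strongest reply is that drop-out may mean only that the practice leaves trial procedures. The KCCQ comes from telephone interviews by trained staff, separate from the practices' own data entry, so enrolled patients could still be interviewed and analysed as randomised. The full protocol or SAP may say so. This stands as far as it goes: a reader might infer that the article flatly contradicts itself, but it never says that data are discarded. What remains is that the article fixes a drop-out rule, budgets dropped practices as lost clusters and promises intention-to-treat without connecting the three.

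The trigger is also narrow. Telemonitoring is described as a benefit "which is reimbursed by statutory health insurance since January 2022 for patients with NYHA functional class II or III and guideline-based treatment", and a reader might infer that the rule strips out good usual care in general. It does not: the HF-MPA must hold an active interface role, and telemonitoring without that role does not meet the definition. The rule is aimed at contamination. But that narrowness is also why the excluded care resembles the intervention so closely.

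The lack of a counterpart in the intervention arm is largely inherent, since those practices are meant to run such a pathway. This explains the asymmetry but does not remove its effect on the comparison.

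A reader might also infer a loss of power. Taking five control practices from 25 versus 25 gives 74.7%, but 25 per arm is already net of the planned 10% practice drop-out. From the 28 and 27 practices enrolled, losing five controls leaves 28 versus 22 and 79.2% on the same inputs. A power objection is not supported.

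Finally, the article reports seven withdrawals (four intervention, three control), all before patient recruitment and for lack of staff or time. None is attributed to this rule. It also does not say that joining the DMP-HI triggers drop-out, so depletion of the DMP-HI sensitivity analysis is only a possibility.

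**Conclusion.** The point holds in conditional form. The article states a post-allocation drop-out rule for the control arm only, triggered by care that closely resembles the intervention, and does not reconcile it with the promised intention-to-treat analysis. If dropped practices' data are excluded, the primary comparison is no longer the randomised one. On the trial's own hypothesis that such care improves KCCQ-OSS, the exclusion would tend to favour HI-PLUS, by about 0.25–1.25 points over the assumed ranges, against a target of 5.

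A reader might infer that bias toward the intervention is established. It is not. The bias is zero if the pathway has no effect and adoption is unrelated to outcome, and it could reverse if adopting practices do worse. The document gives no trigger rate and reports no practice that met the trigger, so the actual size is unknown and could be nil. The rule still needs correcting before analysis, because followed as naturally read it would break the randomised comparison.

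**What to change.** - Replace the drop-out trigger with a rule that every randomised control practice and all its enrolled patients stay in follow-up, including the 12-month telephone KCCQ, and are analysed as allocated in the primary analysis, whatever pathway the practice adopts.
- Use the quarterly survey to record the date of pathway adoption and to describe contamination.
- Confine any exclusion or censoring of adopting practices to a supplementary analysis labelled as not intention-to-treat.
- Apply any eligibility check for an already implemented pathway before allocation and identically to both arms. Allocation in this trial is complete, so here this means stating when and how the check was made in each arm.

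The cost is wording in the protocol and SAP; the telephone interviews already exist. The article puts the last follow-up visit in June 2026, so any affected practice's patients not yet at 12 months can still be interviewed if this is settled before then. The downside is that the effect estimate may be slightly smaller because contamination stays in the control arm.
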